## Abstract

**Background:**

One strategy to prevent adverse effects resulting from chemotherapy treatment is to perform physical exercises during treatment. However, there is still no consensus on the best type and intensity of exercise, nor when it should be started. Most studies have been carried out in patients with breast cancer, usually a few weeks after starting chemotherapy, on an outpatient basis 2 to 3 times a week. The main differences in our study are that we carried out physical training in hospitalized patients undergoing a cycle of chemotherapy for cancer treatment and that this training was carried out 5 times a week and was not restricted to a specific type of cancer.

**Objective:**

We aimed to evaluate the effects of aerobic training on symptoms related to chemotherapy (nausea, vomiting, asthenia, and sensation of weakness), fatigue, mobility, clinical complications, and length of hospital stay of patients during the drug treatment cycle. We also evaluated patient satisfaction with the proposed intervention, the adverse effects of aerobics training, and the cost-effectiveness of this intervention.

**Methods:**

This is a controlled and randomized trial with blinded evaluation that will include 94 hospitalized patients with cancer for 1 or more cycles of chemotherapy. The intervention group will perform aerobic training during a cycle of chemotherapy. The control group will receive a booklet with guidelines for staying active during the hospitalization period. The groups will be compared using a linear mixed model for fatigue, mobility, and chemotherapy-related symptoms before and after the intervention. The length of hospital stay will also be compared between groups using Kaplan-Meier survival analysis. The incidence of complications will be compared using the *χ*^2^ test. Cost-effectiveness and cost-utility analyses will be performed for the impact of exercise and quality-adjusted life years with the EQ-5D-3L-21 quality of life trials. The implementation variables (acceptability, suitability, and feasibility) will be evaluated by frequencies.

**Results:**

The clinical trial registration was approved in March 2023. Recruitment and data collection for the trial are ongoing, and the results of this study are likely to be published in late 2025.

**Conclusions:**

Chemotherapy has side effects that negatively impact the quality of life of patients with cancer. Aerobic exercise can reduce these side effects in a simple and inexpensive way. The field of work of physical therapists could be expanded to oncology if the intervention works.

**Trial Registration:**

Registro Brasileiro de Ensaios Clínicos RBR-6b4zwx3; https://tinyurl.com/39c4c7wz

**International Registered Report Identifier (IRRID):**

DERR1-10.2196/60828

## Introduction

Cancer is already the biggest public health problem in the world. In Brazil, the estimate for the 2023-2025 period is that there will be 704,000 new cases of cancer per year (excluding cases of nonmelanoma skin cancer) [1]. One of the main forms of treatment for cancer is chemotherapy, which consists of a systemic treatment in which a drug is used to interfere with cell proliferation, targeting its DNA or RNA and its metabolism [2]. The costs of cancer treatment in the United States already reach US $158 billion per year [3], and in Brazil, they exceed R $3.5 billion (US $700 million) [4]. The application of these resources requires health care staff, medications used directly and indirectly in treatment, equipment, and hospitalization days.

Treatment with chemotherapy involves a series of side effects, including nausea, vomiting, diarrhea, and febrile neutropenia, which are treated with supplementary medications. These adverse effects have a major impact on patients’ lives, as well as on adherence and compliance with the recommended dose of treatment, and they are also associated with an increase in the rate of hospitalization. At least one-third of women undergoing adjuvant chemotherapy treatment for breast cancer are unable to complete the prescribed dose of treatment due to adverse effects, thus compromising the prognosis of the disease [5].

Physical exercise in patients with cancer during chemotherapy has been tested in randomized trials [5-11] and appears to improve physical function, fatigue, symptom burden, and the quality of life of patients, in addition to allowing the nonreduction of chemotherapy doses. However, most studies have been carried out on an outpatient basis, involved patients with breast cancer, used 3 weekly exercise sessions, and evaluated fatigue as the primary outcome. There are still no clinical trials testing the effect of exercise in a hospital environment with daily sessions (Monday to Friday) carried out during the chemotherapy cycle.

Therefore, our objective is to evaluate the effects of aerobic training on chemotherapy-related symptoms (nausea, vomiting, asthenia, and sensation of weakness), fatigue, mobility, clinical complications, and length of hospital stay in patients during the drug treatment cycle. Furthermore, we also aim to evaluate the adverse effects of aerobic training, patient satisfaction with the proposed intervention, its implementation, and its cost-effectiveness.

## Methods

### Design

This is the protocol for a randomized controlled trial with 2 parallel groups, 1:1 allocation, and blind evaluation that will be conducted in the oncology ward of the Instituto de Assistência Médica ao Servidor State Public, São Paulo-SP, Brazil, in accord with the CONSORT (Consolidated Standards of Reporting Trials) checklist [12]. The trial has been registered on the Registro Brasileiro de Ensaios Clínicos (RBR-6b4zwx3).

### Ethical Considerations

This study protocol was approved by the research ethics committees of the Universidade Cidade de São Paulo and Instituto de Assistência Médica ao Servidor (50436221.7.3001.5463). All participants will provide written informed consent before participating in this study. This will be collected and stored securely by one of the clinical data collection team members.

### Participants

Patients older than 18 years diagnosed with cancer and hospitalized in the ward to undergo at least 1 cycle of chemotherapy will be eligible for this study. Patients will be included in the study if they do not have musculoskeletal, cognitive, or clinical limitations that interfere with the proposed assessments and interventions, such as heart disease (eg, moderate to severe aortic or pulmonary stenosis, decompensated heart failure, advanced cardiac arrhythmias, myocarditis, and unstable coronary insufficiency), lung diseases (eg, chronic obstructive pulmonary disease or decompensated asthma), diabetes mellitus, and decompensated systemic arterial hypertension with serum hemoglobin <8g/dL or hematocrit <25% or platelets <30,000 mm [5,13-15].

Patients who require transfer to the intensive care unit, or for whom chemotherapy treatment has been contraindicated or discontinued for any reason, will be excluded from the study.

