### Procedures

During the protocol period, all patients admitted to the oncology ward who are identified and meet the eligibility criteria will be invited to participate in the study by the evaluating physiotherapist. These eligible patients will be informed about the objectives of the study and invited to sign the informed consent form. Next, the patients will be evaluated regarding anthropometric and clinical characteristics, fatigue, and mobility, as well as the occurrence, frequency, intensity, and discomfort of the main adverse effects of chemotherapy. After the initial assessment, patients will be randomized into an intervention group, which will perform aerobic exercise sessions, and a control group, which will receive a booklet with guidelines (the same booklet will be given to the patients in the intervention group). The next day, the intervention will begin. Aerobic training will be carried out from Monday to Friday while the patients are hospitalized for the chemotherapy cycle in the oncology ward. Before carrying out the day’s aerobic exercise session, the patients will be asked if they feel any type of discomfort that is related to the previous day’s training (for example, muscle or joint pain in the lower limbs). If for any reason chemotherapy is interrupted for a patient, the exercises will also be interrupted, and as soon as chemotherapy treatment is resumed, the exercise will also be resumed. The booklet will be given to the patients and explained by a trained physiotherapist. Patients will be re-evaluated on the day following the last day of the chemotherapy cycle regarding the occurrence, frequency, intensity, and discomfort of adverse effects of the treatment, as well as fatigue, mobility, and satisfaction with the proposed intervention.

After the study intervention period, patients who need it will receive routine physiotherapeutic care provided by the physiotherapy team at the hospital. The incidence of clinical complications from chemotherapy and the length of hospital stay will be assessed as outcomes until hospital discharge. All data will be collected by a blinded assessor. Additionally, data will be coded and entered into a Microsoft Excel spreadsheet and will be double-checked before analysis. A visual representation of the study design is presented in Figure 1.

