### Randomization

Immediately after baseline assessments and before starting the intervention, patients will be randomly allocated to 1 of 2 groups: intervention or control. The allocation will be conducted by a researcher who will not be involved in the selection or evaluation of patients or in the intervention; it will follow a randomization schedule generated by a website [16] with a 1:1 allocation rate. The rooms in the ward accommodate 2 to 4 patients (beds); therefore, randomization will be carried out by group or cluster [17]. The rooms will be randomized, because although the intervention is directed to one patient, it can affect another patient in the same room, contaminating those who should not receive the intervention and reducing the estimated result [17]. The researcher responsible for randomization will place a written document inside a sealed opaque envelope indicating which group (intervention or control) each room belongs to in order to ensure the confidential allocation of patients to the blinded evaluator [18]. Before starting the intervention, the physiotherapist responsible for the intervention will open the envelope in front of the patient and disclose which group the room the patient is in corresponds to.

Due to the nature of the study, it will not be possible to blind the physiotherapist responsible for the intervention or the patients. However, the evaluator will be blinded to the groups (intervention and control). After the intervention and assessments, the physiotherapist responsible for the intervention will ask the blinded evaluator to which group (intervention or control) he believes each patient belonged to evaluate the evaluator’s blinding.

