Other outcomes will be assessed, such as fatigue, level of patient mobility, length of hospital stay, and clinical complications. Fatigue will be assessed using the Brief Fatigue Inventory, Brazilian version. This inventory consists of 9 items that are rated from 0 to 10 on a visual numeric scale. The first question is a dichotomous question about whether the patient has felt tired or fatigued in the last 7 days. Three items refer to the severity of fatigue at the time of assessment, the usual fatigue in the last 24 hours, and the worst fatigue in the last 24 hours, where 0 represents no fatigue and 10 “the worst fatigue imaginable.” The other 6 items refer to how fatigue interfered with different aspects of the patient’s life in the last 24 hours; these items are “general activities,” “mood,” “ability to walk,” “work” (including work outside and at home and daily tasks), “relationships with other people,” and “enjoying life,” where 0 means that it does not interfere and 10 means that it interferes completely [22,23]. This inventory will be applied in the initial and final assessments by an evaluator blind to which group the patient belongs.

The level of mobility will be assessed using the De Morton Mobility Index. This scale is made up of 15 activities, where 11 are classified as 0 or 1 (incapable or capable, respectively) and 4 are classified as 0, 1, or 2 (incapable, partial, and capable, respectively). Of the 15 activities, 3 are performed in bed, 3 in a chair, 4 involve static balance, 2 involve walking, and 3 involve dynamic balance. The scale was translated and validated in Brazilian Portuguese [24,25] and ranges from a score of 0, which represents low mobility, to 100, which represents high mobility. This index will be applied by an evaluator who is blind to which group the patient belongs and will be applied in the initial and final assessments.

In addition, the total number of days of hospital stay, possible clinical complications (cardiac, pulmonary, infectious, or neurological) arising from chemotherapy treatment, and the need for transfer to the intensive care unit will be accessed through the medical records of the patient.

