### Statistical Design

The calculation to determine the sample size was carried out based on a previous randomized clinical trial that also compared the effect of aerobic training compared to usual care on the deleterious effects of chemotherapy in patients with breast cancer [11]. Our study was designed to detect a difference of 2.7 (SD 4) points in the physical fatigue score, in addition to a difference of 6.2 (SD 7) episodes of vomiting or nausea between the groups. A power of 80%, an α of 5%, and a loss to follow-up of 15% of the sample were considered. A sample of 94 patients (47 patients in each group) was estimated.

After the data collection, all analyses will be conducted following intention-to-treat principles and will be performed by a researcher who will not be involved in the study assessments and intervention.

For analyzing the effect of the intervention, after a descriptive analysis and the Shapiro-Wilk normality test with a visual analysis, the groups will be compared using a linear mixed model for fatigue, mobility, and chemotherapy-related symptoms before and after the intervention. The length of hospital stay will also be compared between groups using Kaplan-Meier survival analysis. The *χ*^2^ test will be used to compare the clinical complication rates between groups. Descriptive analysis will be used for recruitment, completion, and adherence rates and potential adverse events. The significance level will be set at 5%. For all these analyses, SPSS (version 21.0; IBM Corp) will be used.

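### The exclusion of patients who go to intensive care or stop chemotherapy has no time point; applied after allocation it conflicts with intention-to-treat and selectively removes severe cases

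*Protocol article*

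**What the plan says.** Five statements in the protocol article's Methods bear on this point.

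- **Participants:** "Patients who require transfer to the intensive care unit, or for whom chemotherapy treatment has been contraindicated or discontinued for any reason, will be excluded". The sentence ends by saying that the exclusion is from the study. It names no time point and does not say what happens to data already collected.
- **Randomization:** "Immediately after baseline assessments and before starting the intervention, patients will be randomly allocated to 1 of 2 groups". Under Procedures, training begins on the day after that.
- **Assessments:** next to days in hospital and clinical complications, "the need for transfer to the intensive care unit will be accessed through the medical records of the patient".
- **Procedures:** "The incidence of clinical complications from chemotherapy and the length of hospital stay will be assessed as outcomes until hospital discharge".
- **Statistical Design:** "all analyses will be conducted following intention-to-treat principles". For complications, a chi-square "test will be used to compare the clinical complication rates between groups"; length of stay is compared by Kaplan-Meier analysis.

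Procedures also covers temporary stops: "If for any reason chemotherapy is interrupted for a patient, the exercises will also be interrupted, and as soon as chemotherapy treatment is resumed", exercise resumes as well. No sentence says that an excluded patient stays in follow-up or in any analysis set.

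**The concern.** Needing intensive care and stopping chemotherapy are things that can happen to a patient because of the treatment received. The protocol's own reasoning puts them on the causal path. The Introduction says that adverse effects reduce adherence to the chemotherapy dose and that exercise appears to help keep doses up. It then hypothesises fewer symptoms, fewer complications and shorter stays with exercise. Dropping patients on such events after allocation conditions the comparison on a possible effect of the intervention, and the two groups are no longer those that randomisation made.

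Three things are at stake. The complication, length-of-stay and cost comparisons lose their most severe cases. The primary MSAS-BR comparison may lose its most symptomatic patients, since toxicity is a plausible reason for stopping chemotherapy. And if exercise led some inpatients to deteriorate and need intensive care, the rule would remove exactly those patients from view.

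**Working it through.** **Timing.** Baseline assessment, then randomisation, then training from the next day, then final assessment on the day after the cycle ends, then records to discharge. Eligible patients are already inpatients admitted for chemotherapy. A contraindication could be found before randomisation. Transfer to intensive care and discontinuation are events of the stay, and most of the stay lies after allocation. That the exclusion acts after randomisation is therefore a strong inference, not stated text.

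**Side by side, if it acts after allocation.** Intention-to-treat keeps every randomised patient; the exclusion removes some of them. The records are to show who needed intensive care; everyone who did is out of the study. With all such patients removed, the analysed ICU count is 0 in both groups whatever the true rates.

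**Inputs.** From Statistical Design: 47 per group; fatigue difference 2.7, SD 4; 80% power; 5% alpha; 15% loss. The protocol gives no complication, ICU or discontinuation rates, so every rate or count below is an assumption.

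**Complications, same excluded share in both arms.** Let p be the true rate and f the share of patients with a complication who are excluded. The rate among those left is p(1 − f)/(1 − pf). With p = 30% (control) and 15% (exercise):

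| f | Control | Exercise | Difference (points) | Chi-square power |
|---|---|---|---|---|
| 0 | 30.0% | 15.0% | 15.0 | 41% |
| 25% | 0.225/0.925 = 24.3% | 0.1125/0.9625 = 11.7% | 12.6 | 34% |
| 50% | 0.150/0.850 = 17.6% | 0.075/0.925 = 8.1% | 9.5 | 25% |
| 75% | 0.075/0.775 = 9.7% | 0.0375/0.8875 = 4.2% | 5.5 | 15% |

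Power starts from 47 per arm less the exclusions and ignores the clustering by room.

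**Complications, share differing by arm.** Take 10/47 control and 6/47 exercise patients with a complication: 21.3% vs 12.8%, a difference of 8.5 points.

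- 5 of the control and 1 of the exercise cases excluded: 5/42 = 11.9% vs 5/46 = 10.9%, difference 1.0 point.
- 1 of the control and 5 of the exercise cases excluded: 9/46 = 19.6% vs 1/42 = 2.4%, difference 17.2 points.

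The same true difference can nearly vanish or double.

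**Length of stay.** Assume a mean of 20 days with ICU transfer and 7 without. With ICU rates of 10% vs 5%, the means are 0.9 × 7 + 0.1 × 20 = 8.30 and 0.95 × 7 + 0.05 × 20 = 7.65, a difference of 0.65 days. With 20% vs 10% it is 9.6 − 8.3 = 1.3 days. After exclusion it is 0 in both cases, because the example places the whole difference in ICU patients.

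**Power.** The plan's only computed figure is its sample size. From the fatigue inputs, 2 × (1.960 + 0.842)² × 4²/2.7² = 34.5, so 35 per arm; 35/0.85 gives 42, total 84 (86 with the t distribution). This does not reproduce 94, but that is a separate matter and nothing here rests on it. Fatigue power, Φ(2.7/(4√(2/n)) − 1.96), is 90.5% at n = 47 and 85.5% after 15% loss (n = 40). If exclusions of 10%, 15% or 20% come on top of that loss, it is 82%, 79% or 77%, again ignoring clustering. Bias is the larger harm; loss of power is secondary. The effect on MSAS-BR cannot be sized, because the protocol gives no variance for it.

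**The case against.** The strongest reply is that the sentence stands under Participants, directly after the eligibility list, and may be meant for screening. Alternatively, exclusion from the study may mean leaving study procedures only, with the records still followed to discharge and analysed by intention-to-treat. Both readings are coherent, and on either one ICU transfers are not lost. Neither is written down, however. The plain words, applied to events during the stay, remove the patient. What stands of the reply is that the timing must be called an inference, and that the repair is largely one of clarification.

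A reader might go further and infer that the protocol expressly orders exclusion after randomisation and so deletes its complication, ICU and length-of-stay outcomes altogether. The text does not support that. No time point is given, and only ICU transfer would be lost completely. It is a collected item without a named test and is not among the stated objectives. Complications and stay remain for all other patients, with the severe end selectively cut off.

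A reader might also see a direct contradiction with the rule that "as soon as chemotherapy treatment is resumed, the exercise will also be resumed". That rule concerns an interruption, the exclusion a discontinuation. A pause and a permanent stop can coexist; what is missing is the boundary between them.

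Finally, the numbers are assumed, and the 5-to-1 split is an extreme one. With equal shares excluded, the result is attenuation, not erasure. Even with everyone kept, 10/47 vs 6/47 is far from significant (z about 1.1, p about 0.27). The examples show how the rule distorts an estimate, not that the trial would otherwise have detected that effect.

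**Conclusion.** The concern holds in a conditional form. If the exclusion is applied after allocation, which is the likelier reading, it is incompatible with intention-to-treat. It empties the ICU-transfer item and selectively truncates complications, stay and costs; it may also bias the primary symptom comparison. Because the protocol expects exercise to influence these events, the loss may differ by arm and can hide benefit or harm.

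The size is unknown. The shrinkage from 15 points to between 12.6 and 5.5 assumes true rates of 30% vs 15% and equal excluded shares; unequal shares can push the difference either way. The finding itself rests on the wording and the order of events, not on these figures. It should be corrected before analysis, and soon, since the Results section says that recruitment is under way.

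**What to change.** - State that the ICU and chemotherapy criteria apply only before allocation.
- State that every randomised patient stays in the intention-to-treat set, in the arm of the room to which they were allocated, including after leaving that room.
- Take ICU transfer, complications, stay and costs from the records to discharge for all of them. Retrieve the same data for anyone already excluded after allocation.
- Record ICU transfer and chemotherapy discontinuation as outcomes or intercurrent events.
- Obtain MSAS-BR, BFI and DEMMI where possible, and say when patients who discontinue are assessed, since the final visit is tied to the end of the cycle. Where a score cannot be obtained, treat it as missing in the planned mixed model. Add a sensitivity analysis, because missing at random is doubtful for these patients.
- State any use of multiple imputation or a per-protocol set for the clinical outcomes. The Statistical Design section plans both only for the economic evaluation.
- Reconcile *discontinued* (Participants) with *interrupted* (Procedures). When exercise or chemotherapy stops or resumes remains for the investigators; no clinical rule is changed here.

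The cost is mainly protocol wording and one added sensitivity analysis. Records-based follow-up to discharge is already planned, so there is little extra data work.
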